### Sample size

On the basis of findings of recent meta-analyses of both truant SA [10] and SR SA [11], we expect to find a standardized effect size regarding SA in the range of 0.46–0.54. The targeted sample size is 70 per condition to provide sufficient statistical power (0.80) and a significance level (0.05, two-tailed) to find a generalized effect size regarding SA of 0.54. Similar RCTs have a mean attrition rate of 10% [44–47]; therefore, 80 participants are included in each condition (B2S *n* = 80, TAU *n* = 80).

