#### Primary study parameters

Mixed linear models (MLMs) will be used to compare groups (B2S and TAU) over time (T1, T2, T3) for all recurrent outcome variables. Later, the same analyses will be performed for the follow-up period (T3, T4). MLMs will be used to measure main effects of group and time and the time × group interaction effects. MLMs tolerate missing values and thus do not unnecessarily compromise statistical power [48]. All MLMs will be estimated with the maximum likelihood method and based on the intention-to-treat sample. All models will include a random intercept, and the slope will be specified as random if improving the model fit evaluated by a significant change in the -2 log-likelihood (- 2LL) fit statistics [49]. A visual inspection of the data and an inspection of the model indices for the time variable will determine the best fit for the time variable. The outcomes of specific problems of relevance in the corresponding subgroups having anxiety, depression symptoms, or behavior problems as their primary problems will be explored.

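### The data-driven choice between random intercept and random slope does not guarantee correct standard errors at single visits; a T1-to-T2 contrast could run at about 6–12% under some correlation patterns

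*Protocol article*

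**What the plan says.** The Primary study parameters section of the protocol article plans mixed linear models comparing B2S with TAU over T1, T2 and T3 for all repeatedly measured outcomes. The effects of interest are group, time and their interaction. A random intercept is always present. For the slope, "the slope will be specified as random if improving the model fit evaluated by a significant change in the -2 log-likelihood". Estimation is fixed too: "All MLMs will be estimated with the maximum likelihood method and based on the intention-to-treat sample". The form of the time variable is to be settled by plotting the data and looking at model fit.

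The section names no other covariance structure and no robust standard error. It also singles out no T1-to-T2 contrast as a test. The Sample size section sets the nominal level: "a significance level (0.05, two-tailed". The article gives no standard deviations or between-visit correlations for any outcome.

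**The concern.** Three visits have six variances and covariances. A random intercept alone describes them with two parameters (equal variances, equal correlations). A random intercept plus slope uses four. The plan tests one against the other on the trial data and keeps the smaller structure unless the test is significant.

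Treatment falls between T1 and T2, and T3 is a 3-month follow-up, so it is plausible that T2 and T3 resemble each other more than either resembles T1. With a slope linear in visit number, neither structure reproduces that pattern, and choosing between them does not repair it. The standard error of the T1-to-T2 difference in change, which is the natural end-of-treatment reading, would then be too small. The rule covers the primary outcome and every secondary outcome followed in both arms, and different outcomes could end up with different covariance models.

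**Working it through.** **The plan's own figures.** The relevant figure is the two-sided 5% level. The sample size does not drive this point, because the error below persists however many children are recruited. For the record, "The targeted sample size is 70 per condition" is not reproduced: with 80% power and an effect of 0.54, n = 2 × (1.96 + 0.8416)² / 0.54² = 53.8, so 54 per arm. The gap is on the conservative side and has no bearing here.

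**Inputs.** From the article: three visits, 80 randomised per arm, 5% two-sided, and the rule above. Assumed: the correlations r12, r13, r23, unit variances unless stated, and a categorical group-by-visit mean. With complete data the estimates are differences of arm means, so only the standard error depends on the covariance model.

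**Step 1: what each structure implies.** Write v for variances and c for covariances. The true value is Var(T2−T1) = v1 + v2 − 2·c12.

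- *Intercept plus linear slope (0, 1, 2).* T2−T1 = (T3−T1)/2 − D/2, with D = T1 − 2·T2 + T3. The model treats the fitted line and the curvature D as uncorrelated, so it implies true variance − (c23 − c12) + (v3 − v1)/2.
- *Intercept only.* It implies 2 × (mean variance − mean covariance).

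**Step 2: one case in full, (.4, .4, .8).**

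- True: 2 × (1 − .4) = 1.20.
- Slope model: 1.20 − (.8 − .4) = 0.80. Check through its parameters: residual = Var(D)/6 = 2/6 = 0.333; slope variance = 1.2/4 − 0.333/2 = 0.133; 0.133 + 2 × 0.333 = 0.80. SE ratio √(0.80/1.20) = 0.816, so 18% too small. Size = 2 × [1 − Φ(1.96 × 0.816)] = 11.0%.
- Intercept only: 2 × (1 − 1.6/3) = 0.933. SE ratio 0.882, so 12% too small. Size 8.4%.

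Adding the slope makes this contrast worse, so the −2LL step is no safeguard.

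**Step 3: other cases, T1-to-T2 contrast.** The last column applies the plan's rule (2-df likelihood ratio test at 5%) in simulated null trials. The three values come from separate simulations: 80 per arm with 2,000 runs, 70 per arm with 1,400 runs, and 80 per arm with 1,000 runs. A dash means the case was not run.

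| r12, r13, r23 | True variance | Slope model implies | Large-sample size, slope model | Simulated size under the rule |
|---|---|---|---|---|
| .5, .45, .6 | 1.00 | 0.90 | 6.3% | 6.6%, –, 7.5% |
| .5, .5, .7 | 1.00 | 0.80 | 8.0% | 8.2%, 7.9%, 8.1% |
| .4, .4, .7 | 1.20 | 0.90 | 9.0% | 8.0%, 9.4%, 9.3% |
| .4, .4, .8 | 1.20 | 0.80 | 11.0% | 11.6%, –, 12.1% |
| .3, .3, .8 | 1.40 | 0.90 | 11.6% | 11.8%, 13.3%, 13.5% |

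A separate mixed-model run with 10% dropout at (.4, .4, .7) gave 9.0%. An unstructured covariance gave 4.4–6.0%, 5.1–6.1% and 5.1–6.8% in the three sets. The upper values are in the runs with Wald z tests, which themselves run slightly above 5%.

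**Step 4: where the inflation is absent.** The slope-model bias vanishes when c12 = c23 and v1 = v3. Equal correlations and AR(1) both satisfy this, and simulation agrees: 5.6–5.7% for equal correlations, 4.9–5.0% for AR(1). If (v3 − v1)/2 exceeds c23 − c12, the sign reverses and the test is conservative; checks of such patterns gave 2–3%.

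**Step 5: the tests the article does name.** Under the same rule the overall 2-df group-by-time test ran at 4.5–7.6% and the linear time-by-group test at 5.0–7.0% across the simulations. Most of these values are within a point or two of nominal.

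**The case against.** The strongest objection is that a random slope's covariance depends on how time is coded, and the article leaves that coding to model fit. Under a step coding (0, 1, 1) the same four-parameter model reproduces (.4, .4, .8) exactly. With residual .20, intercept variance .80, slope variance .80 and intercept–slope covariance −.40, cov12 = cov13 = .80 − .40 = .40, cov23 = .80 − .80 + .80 = .80, and Var(T2−T1) = .80 + 2 × .20 = 1.20. When the best-fitting of linear, log and step coding was used, the T1-to-T2 size fell to 5.1–6.8%, level with unstructured. This stands, so it would be wrong to say that neither permitted structure can fit a pre-post trial. But the article lists no candidate codings, log coding alone still gave 7.5–12.4%, and the step coding would be reached only if the analyst happened to try it.

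It is also fair that the article names no T1-to-T2 test and gives no correlations. Both points stand and limit the size of the concern.

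A reader might infer from "Later, the same analyses will be performed for the follow-up period (T3, T4") that the rule breaks down at follow-up, since intercept, slope, their covariance and residual are four parameters for three observable moments. That has no consequence: the random intercept remains, and with two visits it reproduces the variance of the change.

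A reader might also argue that the entry rule of more than 10% absence cuts the T1 variance and worsens the inflation. The article does not show such a cut, and the formula points the other way. With a T1 standard deviation of 0.8 at (.4, .4, .7), the large-sample size is 8.0% rather than 9.0%.

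**Conclusion.** The concern holds in conditional form. The article fixes a data-driven rule that does not guarantee correct standard errors for visit-specific group differences. If T2 and T3 correlate more with each other than with T1, if the random slope is linear in time, and if a T1-to-T2 contrast is read as the end-of-treatment effect, its type I error is about 6–12% rather than 5%. Individual simulated values reach 13.5% in the most extreme case, whose large-sample limit is 11.6%. All of this rests on assumed correlations.

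The documents do not support saying that the trial's stated group-by-time test is materially invalid: that test stays at about 5–7%. With complete data the point estimates are unaffected. With the 10% attrition the article expects, likelihood estimates also depend to some degree on the covariance being right. This should be changed because the remedy is cheap and removes the dependence on unknown correlations. It is not a fatal flaw.

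**What to change.** Replace the −2LL rule with a prespecified unstructured within-child covariance across T1, T2 and T3 for all two-arm outcomes, whatever coding of time is fixed for the means. Fit it by REML with small-sample degrees of freedom (for example Kenward-Roger). State a fallback in case it does not converge, such as heterogeneous Toeplitz, then compound symmetry with robust standard errors.

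The cost is about two sentences of analysis text and two more covariance parameters than the slope model (6 against 4), which is negligible with 160 children. Some standard errors will be slightly larger. In return, standard errors are right for every visit contrast and all outcomes share one covariance model.

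### The coding of time in the primary model is chosen from the trial's own outcome data, not stated to be arm-blind, and neither group nor time × group is named as the decisive test, so the stated 5% level is not secured

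*Protocol article*

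**What the plan says.** All of this is in the Protocol article.

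- **Effects to be estimated** (Primary study parameters): "MLMs will be used to measure main effects of group and time and the time × group interaction effects". The models cover T1, T2 and T3; a later analysis covers T3 and T4. No effect and no visit is named as decisive.
- **Form of time** (same section): "A visual inspection of the data and an inspection of the model indices for the time variable will determine the best fit". The text does not say whether the inspection is by arm or pooled, which forms are candidates, or which index is used.
- **Random slope** (same section): "the slope will be specified as random if improving the model fit evaluated by a significant change" in the -2 log-likelihood.
- **Error level** (Sample size): "a significance level (0.05, two-tailed").
- **Primary hypothesis** (Background, last paragraph): B2S is expected to be superior to TAU in improving attendance. This leans towards a difference in change but names no model term or visit.

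**The concern.** In a group-by-time model the coding of time is part of the hypothesis. Linear time tests a difference in slopes, a pre/post step tests a difference between baseline and the later visits together, and categorical time tests any difference in profile on two degrees of freedom. If the coding is settled after looking at outcomes, and the look can show how the arms diverge, the form that fits best tends to be the one in which a chance divergence is most visible. The test that follows is then no longer at its nominal level.

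The second freedom adds to the first. With group and time × group both reported and neither designated, a success on either could be presented as support for the primary hypothesis.

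At stake are the error rate of the trial's main superiority claim and the meaning of the estimate attached to it.

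**Working it through.** **Inputs from the article.** Two-sided level 0.05, power 0.80, effect size 0.54, 70 per condition raised to 80 for 10% attrition (Sample size); three visits, random intercept, effects of group, time and time × group (Primary study parameters). With 10% attrition, 80 × 0.9 = 72 per arm.

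**Assumed, because the article gives no figure.** Within-child correlation 0.3 to 0.7, equal between all visits; complete data; candidate forms linear (0, 1, 2), log (log 1, 2, 3), step (0, 1, 1) and categorical; a common trend that is flat, linear, log-like or step-shaped.

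**The plan's own figure.** n per arm = 2(1.960 + 0.842)² / 0.54² = 15.70 / 0.2916 = 53.8, so 54 (55 with the t distribution), not 70. With 70 per arm, power at 0.54 is about 0.89. That mismatch is a separate matter. What is used here is only the 0.05 level that the calculation presupposes.

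**Step 1: the coding changes the quantity tested.** Let the true B2S-TAU differences at T1, T2, T3 be 0, d, d. With equally spaced linear time, the fitted slope is (d − 0)/2 = 0.5d and the mean difference is 2d/3. The fitted differences are:

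- T1: 0.67d − 0.5d = 0.17d
- T2: 0.67d
- T3: 0.67d + 0.5d = 1.17d

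T2 has no weight in the slope, and the line implies a baseline difference that does not exist. Categorical coding returns 0, d, d.

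**Step 2: two routes to a claim.** With equal correlations, the group effect rests on child means and the interaction on within-child deviations, so the two tests are close to independent. The chance that at least one is significant under the null is 1 − 0.95² = 0.0975. Simulation gives 9.2-10.0%.

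**Step 3: choosing time by fit.** Simulated null trials (40,000 per scenario at 70 and 80 per arm, repeated at 72), with the form picked by the index and the result then tested at 0.05:

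| Rule | Type I error |
|---|---|
| One pre-fixed form, interaction only | about 5% (linear 4.5-5.0%, categorical 4.9-5.1%) |
| Form chosen on pooled, arm-blind data, interaction only | about 5% |
| Form chosen by BIC, interaction in the model | about 5-8% |
| Form chosen by AIC, interaction in the model | about 7-9% |
| Pre-fixed form, group or interaction counts | about 10% |
| Form chosen by AIC or BIC, group or interaction counts | about 10-13% |

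The upper ends occur when there is no common trend, because chance differences between arms then drive the choice of form. With a clear common trend, BIC stays close to 5% and AIC near 7-8%.

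**The case against.** **Selection is by fit, not by p-value.** This is correct, and it limits the size of the problem. A reader might infer that the analyst will take the most favourable coding and that the primary test is therefore simply not a 5% test. The article states no such rule, and on pooled data selection by fit costs nothing. What stands is that the article does not confine the inspection to pooled data, and selection by fit alone can then inflate the error.

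**The hypothesis points to time × group.** Improvement in attendance, in a mixed between-within design, does suggest the interaction. A reader might also count three competing effects, but the main effect of time does not compare treatments, so there are two. The 10% figure holds only if a group effect alone would be accepted as success, which the article neither says nor excludes.

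**Detail of this kind belongs in an SAP.** That would answer an omission. Here the article positively states a data-dependent rule, and an SAP that fixed the coding in advance would depart from it.

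**Visit times may vary.** Six of the sessions may be weekly or fortnightly (Back2School program), so time to T2 may differ between children and continuous time can be defended. That is a reason to prespecify a continuous form, not to choose one from the outcomes.

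**Points not relied on.** A reader might argue that the group main effect dilutes the effect by including T1, with 75% power against 96% for a baseline-adjusted T2 contrast (72 per arm, correlation 0.5, effect 0.54 at T2 and T3). That comparison leaves out the interaction tests. Under the same assumptions they have about 90% (linear), 93% (categorical) and 96% (pre/post). Moreover, with time coded zero at T1 the group coefficient is a baseline difference, not an average. The random-slope rule is a pre-stated criterion, and its effect on error was not quantified.

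**Conclusion.** The point holds in a conditional form. The article lets outcome data set the coding of time without an arm-blind restriction, and it leaves open which of two treatment-related effects decides the primary hypothesis. If the form is chosen by fit with the interaction in the model, the error rate is about 7-9% (AIC) or 5-8% (BIC) against the stated 5%. It is about 10% if either effect may count as success, and about 10-13% with both freedoms. If the form is chosen on pooled data and only the interaction counts, there is no inflation.

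These figures rest on the assumed correlation, candidate forms, trends and complete data. The two gaps in the text do not depend on them. The documents do not support saying that the test necessarily exceeds 5%, or that T2 in particular must be the primary visit. The change should be made because it is cheap and protects the main claim.

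**What to change.** Before any look at outcomes by arm:

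1. Replace the sentence on inspecting the data with a fixed coding. With three planned assessments, categorical T1, T2, T3 is the natural choice; three means per arm then describe the course without a search for a curve.
2. Name one group × time contrast as the primary test of attendance: the baseline-adjusted B2S-TAU difference at one visit, chosen by the sponsor and stated.
3. Label the group main effect as supportive, and other forms of time as supportive or exploratory.

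If an SAP already does this, record that it supersedes the article's wording. Fixing the coding alone is not enough: while either effect may count, the error stays near 10%.

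The cost is wording only. The sample size is unchanged, and the interaction test returns to about 5%. The one statistical price is a slight loss of efficiency if a prespecified linear trend would have been correct.

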#### Mediators

To test the hypothesis that the effects of the SA are mediated by the mediators investigated (i.e., internalizing and externalizing problems and self-efficacy), analytic steps outlined by MacKinnon et al. will be followed [50, 51].

## Discussion

Developing an effective intervention for children with SA is critically important because there are a great number of school-aged children who struggle to attend school regularly. The complex nature of SA is often handled with equally complex and unsystematic approaches. This makes it difficult for families to navigate and find the help that fits their situation and problems. There is a lack of systematic approaches for helping youths with SA, which can be tailored to fit the presenting problems of the youths and families that struggle with SA. The present study will provide information about the effectiveness of the manualized transdiagnostic multimodal CBT intervention B2S for treating SA. If the intervention is found to be efficacious, it could be a subject for large-scale implementation in school health services. The systematic program may be easier to implement by health professionals and provide better help for these youths and their families, but it needs to be compared with and found superior to the TAU intervention before such a conclusion can be drawn. In the present study, sound psychometric measures are used with multiple respondents in a study with an RCT design. The two conditions are studied with conditions that closely match a real-world setting.

### Trial status

A feasibility study of 24 children was performed in the spring of 2017, with high satisfaction scores and a low dropout rate. Based on the experiences from the feasibility study, the treatment manual and some of the procedures were revised. The present protocol is version 2, October 23, 2018. Inclusion of participants to the RCT started September 4, 2017. Inclusion is expected to be finished by September 4, 2019 (Additional file 1).

## Abbreviations

B2S: Back2School
CBT: Cognitive behavioral therapy
CEBU: Center for Psychological Treatment for Children and Adolescents
CHU-9D: Child Health Utility 9D Index
EBT: Evidence-based treatment
ESQ: Experience of Service Questionnaire
FAD: Family Assessment Device
M: Aarhus Municipality
MFQ: Mood and Feelings Questionnaire
MLM: Mixed linear model
MMM: Mind My Mind
P: Parent
PECK: Personal Experience Checklist
QED: Quasi-experimental design
RCT: Randomized controlled trial
SA: School absenteeism
SAP: School attendance problem
SCAS: Spence Children’s Anxiety Scale
SDQ: Strength and Difficulties Questionnaire
SEQ-RSAP: Self-Efficacy Questionnaire for Responding to School Attendance Problems
SEQ-SS: Self-Efficacy Questionnaire for School Situations
SR: School refusal
SRAS-R: School Refusal Assessment Scale–Revised
SW: School withdrawal
T: Teacher
TAU: Treatment as usual
TR: Truancy
Y: Youth
